1. DATA MANAGEMENT AND STATISTICAL ANALYSIS
   1. Sample Size Calculation and Justification

To determine the number of subjects required to test the hypothesis relating to the primary variable (proportion of subjects with seroconversion on Day 28 after vaccination), the following conservative assumptions are used:

- study power is about 90 %
- two-sided significance level (alpha) is 5 %; Pocock’s corrected alpha level for multiple comparisons of the primary variable due to an interim analysis is 0.02616 and 0.03039 for the interim and final analysis (performed after obtaining primary variable data for all randomised subjects), respectively
- proportion of subjects with seroconversion in the placebo group is 20 %
- proposed difference between the placebo and vaccine group in terms of the primary variable is 30–60 % (odds ratio is 4–16)
- randomisation ratio between the vaccine and placebo group is 3:1, respectively
- two countries (accrual will be competitive, so a uniform assignment is considered for the calculation)
- dropout from the study/statistical analysis during the observation period of 28 days is about 10 %.

According to the results of the sample size calculation performed using the PASS 12 software (Professional License, NCSS LLC (www.ncss.com)), 180 subjects should be included in the statistical analysis to ensure the power of 90 % for the between-group comparison of the primary variable considering the assumption of 20 % seroconversion rate in the placebo group and the superiority of the vaccine group of at least 30 % (conservative assumption, odds ratio = 4), as well as the corrected two-sided significance level of 0.02616 (one-sided level of 0.01308) and randomisation ratio of 3:1. The number of subjects corresponding to the conservative estimate of differences between the vaccine and placebo groups in terms of the primary variable is chosen to ensure the provision of safety data. Considering the possible dropout from the study/statistical analysis during the observation period of 28 days (10 % of subjects), the number of randomised subjects should be increased up to 200 (in a 3:1 ratio).

To provide more detailed safety and efficacy data (including age subgroups), it is planned to randomise 500 subjects (in a 3:1 ratio [Ad5-nCoV:placebo]). Additionally, the extended sample size will allow to provide descriptive data on exploratory endpoints related to the frequency of confirmed COVID-19 cases within 6 months after vaccination (except for the cases occurred during the first 14 days after vaccination).

Because the study includes an unblinded interim analysis after obtaining a fraction of information (τ = 0.4) for the assessment of the primary variable (based on the data obtained approximately from the first 200 randomised volunteers through Visit 5, including early dropouts before Visit 5) and the Pocock alpha spending function is used, to adjust the significance level due to multiple comparisons of the primary variable (interim analysis), the two-sided alpha level for the interim and final analysis is set to be 0.02616 and 0.03039, respectively (overall two-sided significance level is 5 %). If statistically significant findings of the between-group comparison of the primary variable are obtained during the interim analysis, the study will not be suspended and the interim analysis results will be provided to regulatory authorities for review.

Sample Calculation Results Using PASS 12 — Professional

License, NCSS LLC (www.ncss.com)

**Tests for Two Proportions in a Stratified Design (Cochran/Mantel-Haenszel Test)**

**Numeric Results of Cochran-Mantel-Haenszel Test of an Odds Ratio**

**H0: OR1 = OR0. H1: OR1 > OR0.**

|  | **Total**  **Sample**  **Size** | **Sample**  **Size**  **Multiplier** | **Sample**  **Size of**  **Group 1** | **Sample**  **Size of**  **Group 2** | **H0**  **Odds**  **Ratio** | **Actual**  **Odds**  **Ratio** |  |  |
| --- | --- | --- | --- | --- | --- | --- | --- | --- |
|  |  |  |  |  |  |  | **Signif.**  **Level** |  |
|  |  |  |  |  |  |  |  |  |
| **Power** | **(N)** | **(M)** | **(N1)** | **(N2)** | **(OR0)** | **(OR1)** | **Alpha** | **Beta** |
| 0.9000 | 178 | 178.045 | 134 | 45 | 1.000 | 4.000 | 0.0131 | 0.1000 |
| 0.9000 | 134 | 133.703 | 100 | 33 | 1.000 | 4.900 | 0.0131 | 0.1000 |
| 0.9000 | 104 | 104.278 | 78 | 26 | 1.000 | 6.000 | 0.0131 | 0.1000 |
| 0.9000 | 67 | 67.243 | 50 | 17 | 1.000 | 9.300 | 0.0131 | 0.1000 |
| 0.9000 | 45 | 45.123 | 34 | 11 | 1.000 | 16.000 | 0.0131 | 0.1000 |

| **Strata-Detail Report** | | | | | | |
| --- | --- | --- | --- | --- | --- | --- |
| **Number**  **of**  **Strata** | **Proportion of Total Sample in each Strata** | **Proportion of this Strata in Group 1** | **Proportion of this Strata in Group 2** | **Group 1 Multiplier**  **(R1)** | **Group 2 Multiplier (R2)** | **Strata**  **Probability**  **of**  **Success** |
| 2 | 0.5000 | 0.7500 | 0.2500 | 0.375 | 0.125 | 0.2000 |

Report Definitions

Power: the probability of rejecting a false null hypothesis.

N: the total sample size summed across all groups and strata.

M: the factor by which the values of R1 and R2 are multiplied.

N1 and N2: the sample sizes from groups 1 and 2 summed across all strata.

OR0: the odds ratio [P1/(1-P1)] / [P2/(1-P2)] assuming the null hypothesis (H0). OR1: the value of the odds ratio at which the power is computed.

Alpha: the probability of rejecting a true null hypothesis.

Beta: the probability of accepting a false null hypothesis.

In a treatment vs. control design, the treatment group is 1 and the control group is 2.

Note: Р1 and Р2 are the proportion of subjects with an event in the investigational product group and control group, respectively.

- 1. Statistical Analysis Plan
     1. Statistical Analysis Sets

The following analysis sets will be used:

Randomised Set

This population will include subjects completed the randomisation and allocated into one of the study groups. This population will be used to provide the disposition of study subjects.

Safety Analysis Set

This population will include all randomised volunteers received a dose of the vaccine. It will be used for safety analysis.

Full Analysis Set (FAS, for immunogenicity analysis)

This analysis set will include all eligible volunteers from the safety population with at least one immunogenicity assessment result (for interim analysis, it should be obtained until Visit 5 [inclusive]). This set will be the main population for immunogenicity analysis.

Cellular immune response parameters will be analysed in the FAS subgroup for the analysis of vaccine efficacy including subjects with at least one cellular immunity assessment result.

Per-protocol Set (PPS, for immunogenicity analysis)

The population will include all eligible volunteers from the FAS received a dose of the vaccine according to the randomisation and study scheme and provided data for immunogenicity assessment before and after vaccination in line with the study scheme (for interim analysis, they should be obtained until Visit 5 [inclusive]). Such volunteers should not administer prohibited medications, should not have other major protocol deviations potentially affecting immunogenicity assessment and should not have confirmed COVID-19 cases within 14 days after vaccination. This set will be a supportive population for immunogenicity analysis.

Full Analysis Set (FAS, for efficacy analysis)

The population will include all eligible volunteers from the Safety Analysis Set contacted at least once after Day 14 excluding subjects with confirmed COVID-19 cases within 14 days after vaccination. This set will be the main population for efficacy analysis.

Per-protocol Set (PPS, for efficacy analysis)

The population will include all eligible volunteers from the FAS received a dose of the vaccine according to the randomisation and study scheme. Such volunteers should not administer prohibited medications, should not have other major protocol deviations potentially affecting efficacy assessment and should not have confirmed COVID-19 cases within 14 days after vaccination. This set will be a supportive population for efficacy analysis.

- - 1. General Provisions

A detailed description of statistical methods will be provided in the Statistical Analysis Plan before the database lock. General information on the proposed statistical analysis is provided below.

Descriptive statistics will be provided for all demographic and other baseline characteristics, immunogenicity, cellular immune response, efficacy and safety parameters, as well as their changes (if applicable) during the study by evaluation time points and treatment groups. Demographic characteristics and efficacy endpoints will also be presented by the pre-existing anti-Ad5 neutralising antibody titers (low and negative (≤ 1:200) vs high (> 1:200)). Descriptive statistics for quantitative parameters will include the mean, the standard deviation (SD), the median, the first and third quartiles, the minimum and maximum values and the number of valid observations. The geometric mean values will be also presented for antibody titres and fold-rises in titers. Qualitative data will be presented as rates and percentage. Where applicable, 95 % confidence intervals will also be provided.

For undetermined values of the geometric mean titer, geometric mean fold-rise and seroconversion rate, the following algorithm will be used: 1) if the antibody titer is below the lower limit of quantitation, a half LoD value will be used 2) if the antibody titer is above the maximum limit of quantitation, the maximum dilution will be used.

Missing Data

Only available values will be used for statistical analysis. Missing values will not be imputed.

Procedures for Reporting Any Deviations from the Original Statistical Plan

In the case of any deviations from the planned statistical analysis described in the protocol, the clinical trial report will include the description and justification of implemented changes.

- - 1. Efficacy Analysis

The primary variable will be analysed during the interim and final analysis using the corrected significance level (overall significance level is two-sided 5 %). Secondary variables will be analysed using the two-sided 5 % significance level.

Efficacy variables representing the seroconversion rate (proportion of subjects with at least four-times increase in antibody titers), including the primary efficacy endpoint, will be presented by evaluation time points and treatment groups.

To compare the seroconversion rate (including the primary efficacy endpoint) by evaluation time points, a statistical hypothesis of the statistical superiority of the vaccine against placebo will be tested:

Н_0_: OR = 1 Н_A_: OR > 1

OR = odds ratio: OR = [P_1_/(1-P_1_)] / [P_2_/(1-P_2_)]

P_1_ and P_2_ — proportion of subjects with seroconversion in the vaccine and placebo group, respectively.

The results will be descriptively provided by trial sites and countries. The primary variable will be analysed using the Mantel-Haenszel test with the country as a factor if at the time of the analysis the analysis set in each country will have a proper number of subjects with the assessed primary endpoint (at least 20 % of the planned number of subjects for the interim analysis in the vaccine and placebo groups). Otherwise, data will be analysed using the trial site as a factor. Detailed information about combining data for small trial sites will be presented in the statistical analysis plan. Hypothesis testing will be carried out using the *X* test (or Fisher’s exact test). Corrected and uncorrected two-sided confidence intervals for the percentage differences will be also presented.

Additionally, between-group comparisons will be also performed using logistic regression with the treatment group as a fixed factor, the country as a factor and pre-existing antibody titer as a covariate. Pre-existing anti-Ad5 neutralising antibody titers (low and negative (≤ 200) vs high (> 200)), sex and age will be also considered as potential model factors. Odds ratios will be presented with appropriate 95 % confidence intervals.

Similarly, the proportion of subjects with cellular immune response will be analysed.

Efficacy variable (antibody geometric mean titer (GMT) and neutralising antibody GMT) will be presented and compared by evaluation time points based on the calculated 95 % confidence interval using ANOVA/ANCOVA following the logarithmic transformation of base 10. The ANCOVA model will include the treatment group as a fixed factor, country/trial site as a factor and pre-existing (log-transformed) antibody titer as a covariate. Pre-existing anti-Ad5 neutralising antibody titers (low and negative (≤ 200) vs high (> 200)^1^), sex and age will be also considered as potential model factors. Mean log-transformed differences between the study groups (vaccine/placebo) will be evaluated with the corresponding 95 % confidence interval. The point estimates of the mean differences and the corresponding confidence intervals will be back-transformed.

Efficacy variable (geometric mean fold-rise in antibody titers and neutralising antibody titers) for each treatment group and each antibody GMT evaluation time point will be assessed with the corresponding two-sided 95 % CIs following log-transformation (log10), point estimation of the difference and confidence intervals, and back-transformation of obtained values. Between-group comparisons will be performed using ANOVA/ANCOVA following the logarithmic transformation of base 10. The ANCOVA model will include the treatment group as a fixed factor, country/trial site as a factor and pre-existing (log-transformed) antibody titer as a covariate. Pre-existing anti-Ad5 neutralising antibody titers (low and negative (≤ 200) vs high (> 200)^[[7]](#footnote-7)^), sex and age will be also considered as potential model factors.

Exploratory efficacy endpoints (frequency of confirmed COVID-19 cases during 6 months after vaccination, frequency of confirmed COVID-19 cases requiring hospitalisation, frequency of severe COVID-19 cases, and frequency of lethal COVID-19 cases (except for the cases occurred during the first 14 days after vaccination)) will be presented descriptively by treatment groups. Kaplan-Meier survival estimates will be also presented if applicable.

1. Safety Analysis

The safety analysis will be performed in the safety analysis set using descriptive methods.

Adverse events will be coded using the MedDRA dictionary. The number (proportion) of volunteers with AEs/SAEs and the number of AEs/SAEs will be presented in the form of tables by system organ classes and preferred terms, as well as the relationship to vaccination and severity, and by treatment groups. Upon that, each subject will be counted only once for a system organ class and preferred term with the indication of the relationship to vaccination and maximum severity. The number (percentage) of volunteers with local and systemic immunisation reactions will also be provided.

Laboratory parameters and their changes after vaccination compared to the baseline values, as well as shift tables showing changes with respect to normal values will be tabulated by treatment groups and evaluation time points.

The results of ECG, body temperature and vital signs measurements will be tabulated by treatment groups and each evaluation time point along with changes from the last available measurement before vaccination.

The results of the physical examination will be provided descriptively by treatment groups and evaluation time points.

Serum immunoglobulin E concentration and its changes in 28 days after vaccination compared to the baseline will be tabulated by treatment groups.

1. Interim Analysis

One unblinded interim analysis is planned for the study, which will be performed after obtaining efficacy, reactogenicity and safety data through Visit 5 (Day 28) for the first 200 volunteers randomised in the study. The analysis will be performed by an independent statistician. If statistically significant findings of the between-group comparison of the primary variable are obtained during the interim analysis, the study will not be suspended. The results of the interim analysis will be provided to regulatory authorities to make a decision on the registration of the Ad5-nCoV vaccine.

The final clinical trial report will be prepared after obtaining all data for all volunteers randomised in the study, i.e. after the completion of the final visit by all the volunteers in 6 months after vaccination. The final clinical trial report will be also submitted to regulatory authorities.

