1. STUDY PURPOSE AND OBJECTIVES
   1. Study Purpose

The purpose of the study is the evaluation of the efficacy, reactogenicity and safety of the Ad5-nCoV vaccine compared with placebo in adults aged 18 to 85 years.

- 1. Study Objectives
     1. Primary Objective

The primary objective of the study is to prove the superiority of the Ad5-nCoV vaccine compared with placebo in terms of seroconversion (proportion of subjects with at least four-times increase in antibody titers against the receptor-binding domain [RBD] of the SARS-CoV-2 S protein) on Day 28 after vaccination.

- - 1. Secondary Objectives

1. To evaluate the immunogenicity of the Ad5-nCoV vaccine compared with placebo based on the following:

- Geometric mean titer of serum antibodies against the RBD and SARS-CoV-2 S protein on Day 14, 28 and 6 months after vaccination.
- Seroconversion rate (proportion of subjects with at least four-times increase in antibody titers against the RBD and SARS-CoV-2 S protein) on Day 14, 28 (S protein only) and 6 months after vaccination.
- Geometric mean fold-rise in titers of serum antibodies against the RBD and SARS-CoV-2 S protein on Day 14, 28 and 6 months after vaccination.
- Geometric mean titer of neutralising antibodies against SARS-CoV-2 on Day 14, 28 and 6 months after vaccination.
- Seroconversion rate (proportion of subjects with at least four-times increase in neutralising antibody titers against SARS-CoV-2) on Day 14, 28 and 6 months after vaccination.
- Geometric mean fold-rise in titers of neutralising antibodies against SARS-CoV-2 on Day 14, 28 and 6 months after vaccination.
- Geometric mean titer of neutralising antibodies against the Ad5 vector on Day 28 and 6 months after vaccination.
- Geometric mean fold-rise in titers of neutralising antibodies against the Ad5 vector on Day 28 and 6 months after vaccination.
- Cellular immune response (the number of IFNy-secreting T cells [ELISpot]; percentage of CD4+ and CD8+ T cells expressing IFNy, TNF and IL-2 [flow cytometry]) on Day 14, 28 and 6 months after vaccination.

2. To evaluate the efficacy of the Ad5-nCoV vaccine (exploratory analysis) based on the following:

- Frequency of confirmed COVID-19 cases during 6 months after vaccination (except for the cases occurred during the first 14 days after vaccination).

A confirmed COVID-19 case means the presence of clinical manifestations and a positive laboratory test result for SARS-CoV-2 RNA.

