- Geometric mean titer of neutralising antibodies against SARS-CoV-2 on Day 14, 28 and 6 months after vaccination.
- Seroconversion rate (proportion of subjects with at least four-times increase in neutralising antibody titers against SARS-CoV-2) on Day 14, 28 and 6 months after vaccination.
- Geometric mean fold-rise in titers of neutralising antibodies against SARS-CoV-2 on Day 14, 28 and 6 months after vaccination.
- Geometric mean titer of neutralising antibodies against the Ad5 vector on Day 28 and 6 months after vaccination.
- Geometric mean fold-rise in titers of neutralising antibodies against the Ad5 vector on Day 28 and 6 months after vaccination.
- Cellular immune response (the number of IFNy-secreting T cells [ELISpot]; percentage of CD4+ and CD8+ T cells expressing IFNy, TNF and IL-2 [flow cytometry]) on Day 14, 28 and 6 months after vaccination.

1. Exploratory Efficacy Endpoints

- Frequency of confirmed COVID-19 cases during 6 months after vaccination (except for the cases occurred during the first 14 days after vaccination).

A confirmed COVID-19 case means the presence of clinical manifestations and a positive laboratory test result for SARS-CoV-2 RNA.

- Frequency of confirmed COVID-19 cases requiring hospitalisation (except for the cases occurred during the first 14 days after vaccination).
- Frequency of severe COVID-19 cases (except for the cases that occurred during the first 14 days after vaccination).
- Frequency of lethal COVID-19 cases (except for the cases that occurred during the first 14 days after vaccination).

1. Safety Endpoints

- Reactogenicity (frequency and nature of systemic and local immunisation reactions on the day of vaccination and within 7 days after vaccination).
- Frequency and nature of adverse events (Day 0–Day 28) and serious adverse events (Day 0–Day 28; Day 0–Month 6).
- Vital signs.
- Physical examination results.
- Electrocardiography.
- Biochemistry.
- Haematology.
- Coagulation test.
- Urinalysis.
- Serum immunoglobulin E concentration.

1. Selection and Withdrawal of Subjects
2. Selection of Subjects

A total of 500 subjects aged 18–85 years old will be randomised into the study.

Volunteers will be invited to participate in the trial specifically through advertising. All advertising materials for potential subjects will be initially provided to the ethics committee for approval.

1. Inclusion Criteria

Subjects must meet all of the following criteria to be eligible for participation in the study:

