^1^Within 2 hours after vaccination, the volunteers must be observed at the trial site for systemic and local reactions to the vaccine administration, including immediate hypersensitivity. In 20 minutes (± 5 minutes) and 2 hours (± 10 minutes) after the vaccine administration, the examination of the injection site, body temperature and vital signs measurement, and AEs and concomitant treatment registration will be performed. In 2 hours (± 10 minutes), an additional limited physical examination will be performed. In 5–8 hours after vaccination, the study doctor will contact the volunteer by phone to collect data on AEs and concomitant treatment.

^2^Visit 2 is performed in 48–72 hours after vaccination.

^3^During the collection of medical history at screening, it is necessary to ask the volunteer about the signs and symptoms of COVID-19 (section 8.3) and obtain epidemiological anamnesis (regarding close contacts with persons suspected for SARS-CoV-2 infection or persons with laboratory-confirmed COVID-19 within the last 14 days).

^4^Tests for IgM and IgG antibodies to the N protein and IgG antibodies to the S protein of SARS-CoV-2 at screening and tests for IgM and IgG antibodies to the N protein of SARS-CoV-2 at Visit 5 (Day 28).

^5^Comprehensive physical examination is performed only at screening. At other visits, a limited examination is performed (general appearance, ears, nose, throat, skin and injection site, lymph nodes, cardiovascular system, respiratory system, and neurological system).

| **Study visit** | **Visit 0 (V0)** | **Visit 1 (V1)** | **Visit 2 (V2)** | **Visit 3 (V3)** | **Visit 4 (V4)** | **Visit 5 (V5)** | **Phone contact** | **Visit 6 (V6)** |
| --- | --- | --- | --- | --- | --- | --- | --- | --- |
| **Study day/month** | **Day −10–−1 (screening)** | **Day 0^1^ (vaccination)** | **Day 2 [V1 + 2 days]** | **Day 7 [V1 + 7 days]** | **Day 14 [V1 + 14 days]** | **Day 28 [V1 + 28 days]** | **Month 2 (V5 + 1 month)**  **Month 3 (V5 + 2 months)**  **Month 4 (V5 + 3 months)**  **Month 5 (V5 + 4 months)** | **Month 6 (V5 + 5 months)** |
| Vital signs ^6^ | • | • | • | • | • | • |  | • |
| Body temperature^7^ | • | • | • | • | • | • |  | • |
| Electrocardiography | •^8^ |  | • |  |  |  |  |  |
| Infections^9^ | • |  |  |  |  |  |  | • |
| Haematology^10^, biochemistry^11^, coagulation test^12^, urinalysis^13^ | • |  | • |  |  | • |  |  |
| Blood IgE test | • |  |  |  |  | • |  |  |
| Urine pregnancy test^14^ | • |  |  |  |  |  |  |  |

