Blood analysis for significant infections at screening includes tests for syphilis (Rapid Plasma Reagin), hepatitis B (HBsAg), hepatitis C (antibodies to hepatitis C antigens) and HIV (antibodies to HIV-1 and HIV-2 and HIV-1 and HIV-2 antigens). Repeated HIV test will be performed at Visit 6 (6 months after vaccination).

The tests will be performed at the central laboratory. The investigators will be provided with a separate laboratory manual containing detailed instructions on handling biological samples (collection, storage and transportation).

- - 1. Analysis for IgM and IgG Antibodies to SARS-COV-2

Analysis for serum IgM and IgG antibodies to the N protein and IgG antibodies to the S protein of SARS-CoV-2 will be performed for all volunteers at screening. In the case of the positive result, the volunteer will not be included in the study.

At Visit 5 (Day 28), an additional analysis for IgM and IgG antibodies to the N protein of SARS-CoV-2 will be performed. This analysis is required to detect possible SARS-CoV-2 infection after the volunteer’s enrolment and vaccination.

The analysis will be performed at the central laboratory using the EIA. The investigators will be provided with a separate laboratory manual containing detailed instructions on handling biological samples (collection, storage and transportation).

- - 1. Analysis of SARS-COV-2 RNA (PCR)

The analysis will be performed for all volunteers at screening. In the case of the positive result, the volunteer will not be included in the study. To perform the analysis, a nose and throat swab will be collected by appropriately trained trial site personnel.

If COVID-19 is suspected in the subject during the study, two SARS-CoV-2 RNA tests will be performed with an interval of 3 days (section 8.3).

The analysis for SARS-COV-2 RNA will be performed at the central laboratory using polymerase chain reaction (PCR). The investigators will be provided with a separate laboratory manual containing detailed instructions on handling biological samples (collection, storage and transportation).

Date and time of the smear, analysis results and date should be recorded in the CRF.

- 1. Assessment of Vaccine Efficacy

The list of primary and secondary efficacy endpoints is provided in section 5.3.1.

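### The immunogenicity per-protocol set excludes only COVID-19 in the first 14 days and makes no use of the Day 28 N-antibody result, so titres taken after later infection stay in, chiefly affecting the supportive Month 6 estimates

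*Protocol*

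**What the plan says.** Section 9.2.1 defines two populations for immunogenicity.

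- **Full analysis set (FAS), the main set.** It has no infection rule: "This analysis set will include all eligible volunteers from the safety population with at least one immunogenicity assessment result".
- **Per-protocol set (PPS).** Besides correct dosing, immunogenicity data before and after vaccination, no prohibited medication and no relevant major deviation, its members "should not have confirmed COVID-19 cases within 14 days after vaccination. This set will be a supportive population for immunogenicity analysis".

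Section 8.1.7 adds a laboratory marker of infection: "At Visit 5 (Day 28), an additional analysis for IgM and IgG antibodies to the N protein of SARS-CoV-2 will be performed". It gives the reason: "This analysis is required to detect possible SARS-CoV-2 infection after the volunteer’s enrolment and vaccination". Footnote 4 of Table 14 lists screening tests and then only "tests for IgM and IgG antibodies to the N protein of SARS-CoV-2 at Visit 5 (Day 28"). No set, endpoint definition or analysis in section 9.2 refers to the result.

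On confirmed cases, section 4.2 states: "A confirmed COVID-19 case means the presence of clinical manifestations and a positive laboratory test result for SARS-CoV-2 RNA". Under section 8.3, a swab is prompted by body temperature above 37.5 °C plus at least one further symptom. The same section lets subjects return to scheduled visits after recovery.

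The titre endpoints run to Month 6, for example "Geometric mean titer of neutralising antibodies against SARS-CoV-2 on Day 14, 28 and 6 months after vaccination" (section 5.3.1). RBD and S antibodies have the same Month 6 time point.

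**The concern.** Fourteen days is the window used to discount early cases in the COVID-19 case-count endpoints, and it fits there. For a titre, what matters is whether infection came before the blood draw. A 14-day cut matches only the Day 14 sample. An infection on Day 20 can raise the Day 28 titre, and one in Month 4 can raise the Month 6 titre, yet the PPS keeps both.

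The vaccine expresses the S protein only (section 3.2), so N antibody separates infection from vaccine response. The Phase II summary in section 3.3.2.2 uses N antibody at Day 28 in just this way. Asymptomatic or afebrile infection does not trigger a swab, so the N test is the scheduled means of seeing it, and the analysis sets ignore it.

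No other clause fills the gap. Section 6.5 defines a deviation as a departure from study design or procedures, which an infection is not.

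At stake is how the supportive set is read. Infected placebo subjects raise the placebo GMT and seroconversion rate, and infected vaccinees make persistence look better than it is.

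**Working it through.** **1. The plan's own figure.** The sample size is not in dispute. With 20% vs 50% seroconversion (odds ratio 4), one-sided alpha 0.01308, power 90%, 3:1 allocation and a continuity correction, the two-proportion formula gives 178.04. The PASS output shows 178.045. This becomes 180 evaluable and 180/0.90 = 200 randomised.

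**2. Time left uncovered by the 14-day rule.**
- Before the Day 28 titre: (28 − 14)/28 = 50%.
- Before the Month 6 titre, taking 180 days: (180 − 14)/180 = 92%. Under a constant infection hazard the rule catches 14/180 = 7.8% of infections, and only those that become confirmed cases.

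**3. Day 28 seroconversion.** Assume a share q of each arm is infected (not in the documents) and that every infected subject seroconverts. Each rate p becomes p + (1 − p)q, so the difference becomes (P1 − P2)(1 − q).

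| Case | q | Placebo | Vaccine | Difference | Power, 45 + 135, alpha 0.02616 |
|---|---|---|---|---|---|
| Design | 0 | 20% | 50% | 30.0 points | 93.4% |
| Design | 5% | 24% | 52.5% | 28.5 | 89.1% |
| Design | 10% | 28% | 55% | 27.0 | 83.9% |
| Design | 20% | 36% | 60% | 24.0 | 72.3% |
| Phase II-like | 10% | 10% | 97.3% | 87.3 | about 100% |

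These powers carry no continuity correction. With about 448 evaluable at alpha 0.03039, power in the design case is at least 99.8% for equal q up to 10%. It is 91.3% if 20% of placebo and 10% of vaccinees are infected. The contrast shrinks, so the error is conservative for superiority.

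**4. Month 6 GMT.** If a share q moves from titre a to titre b, GMT = a × (b/a)^q.

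Inputs:
- Uninfected placebo titre 20: half of the Phase II detection limit of 1:40 (section 3.3.2.2), in line with the half-LoD rule in section 9.2.2.
- Post-infection titre 600, uninfected vaccinee titre 150 and q from 5% to 20%: assumptions.

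Placebo inflation is 30^q. With the vaccine GMT held fixed, the ratio is understated by 1 − 30^(−q). With equal infection in both arms, the vaccine GMT is inflated by (600/150)^q = 4^q, and the ratio is understated by 1 − (4/30)^q.

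| q | Placebo inflation | Ratio understated, vaccine GMT fixed | Vaccine-arm inflation | Ratio understated, equal infection |
|---|---|---|---|---|
| 5% | 1.19 | 16% | 1.07 | 10% |
| 10% | 1.41 | 29% | 1.15 | 18% |
| 15% | 1.67 | 40% | 1.23 | 26% |
| 20% | 1.97 | 49% | 1.32 | 33% |

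As a cross-check, take 571 (the Phase II Day 28 GMT at this dose) for both vaccinees and infected subjects. The vaccine GMT then does not move, and the ratio falls from 28.6 to 24.1, 20.4 and 14.6 at q = 5%, 10% and 20%.

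**The case against.** The strongest reply is that little depends on this. The PPS is only supportive, the FAS is the main set, and the contamination works against the vaccine in the between-group test. That stands. A reader might infer that the primary Day 28 result is unsafe; step 3 does not support it. Section 9.1 itself plans for 20% placebo seroconversion, so placebo responses of 5–20% at Day 28 lie within the design assumption.

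A reader might also take 16–49% as the expected bias. It is not. The infected share and the post-infection titre are not in the documents, and the range infects placebo only. Infection among vaccinees offsets part of it, as the last column of step 4 shows.

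Two further inferences go beyond the text.

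- **A prohibited drug in Month 4 removes a valid Day 28 titre.** That is one reading. Section 9.2.1 limits the interim sets to data up to Visit 5, and for the final analysis it does not say whether exclusion is by subject or by visit.
- **The lack of an N test at Month 6 is an error.** The protocol never claims to detect asymptomatic infection at that visit, so adding the test is a design choice.

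Excluding infected subjects has its own weakness. Infection happens after randomisation and the vaccine may affect it, so the remaining arms are no longer a strictly randomised comparison. That is a reason to keep the analysis supportive.

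Finally, section 9.2.2 leaves detailed methods to a statistical analysis plan, which is not shown. The PPS definition, however, is fixed outright in the protocol, and a different rule there would depart from it.

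**Conclusion.** The point holds as a flaw in a stated definition. The PPS already treats infection as a reason for exclusion, but it stops at a date unrelated to the Day 28 and Month 6 titres and leaves unused a test run to detect infection.

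The effect falls mainly on the supportive Month 6 persistence estimates and on the vaccine arm's own GMT and seroconversion rate. Within the assumed inputs, the Month 6 GMT ratio is understated by at most 16–49% (vaccine GMT fixed), or by about 10–33% with equal infection. In the latter case the vaccine arm's GMT is overstated 1.07- to 1.32-fold. At Day 28 the contrast is diluted and the primary conclusion is unlikely to change, provided vaccinees are not infected more often than placebo subjects. This is a low-cost improvement to a supportive set and no threat to the main analysis.

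**What to change.** Define the immunogenicity PPS by visit in section 9.2.1:

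- Exclude a titre at a given visit if a PCR-confirmed case occurred before that visit.
- Also exclude Day 28 and later titres if the Day 28 N-IgM or N-IgG was positive.
- Keep titres taken before the event.
- Apply the prohibited-medication and major-deviation exclusions by visit in the same way, which settles the open reading.
- Keep the FAS as the main set, and report the excluded subjects by arm and reason.

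**Cost.** A change of wording; the case data and the Day 28 N results are already being collected. The Month 6 PPS would hold fewer titres. With 500 × 1/4 = 125 placebo subjects randomised, 5–20% infected is about 6 to 25 placebo subjects. Because exclusion rests on a post-randomisation event that the vaccine may affect, the report should say so and keep the result supportive.

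**Limit.** Infections between Day 28 and Month 6 that are never PCR-confirmed stay undetected. An N assay on serum from the Month 6 visit would narrow that gap. It is an optional addition to the schedule and not part of the required change.
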